**Methods/design:**

This is a phase I trial for patients with malignant pleural mesothelioma with pleural effusion testing the safety of a fixed single dose of 1x10^6^ adoptively transferred FAP-specific re-directed T cells given directly in the pleural effusion. Lymphocytes will be taken 21 days before transfer from peripheral blood. CD8 positive T cells will be isolated and re-programmed by retroviral transfer of a chimeric antigen receptor recognizing FAP which serves as target structure in MPM. At day 0 of the protocol, re-directed T cells will be injected in the pleural effusion and patients will be monitored for 48h under intermediate care conditions. AE, SAE, SADR and SUSAR will be monitored for 35 days and evaluated by an independent safety board to define any dose limiting toxicity (DLT). No further patient can be treated before the previous patient passed day 14 after T cell transfer. The protocol will be judged as save when no DLT occurred in the first 3 patients, or 1 DLT in 6 patients. Secondary objectives are feasibility and immune monitoring.

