**The presence of any one of the following exclusion criteria will lead to exclusion of the subject:**	
Exclusion criteria:	
· Contra-indications to the class of TpP, e.g. known hypersensitivity or allergy to the investigational product,	
· Contra-indications on ethical grounds,	
· Women who are pregnant or breast feeding,	
· Intention to become pregnant during the course of the study,	
· Lack of safe contraception:	
Safe contraception is defined as follows:	
Female and male subjects of childbearing potential, using and willing to continue using a medically reliable method of double barrier contraception for the entire study duration and the next 2 years, such as oral, injectable, or implantable contraceptives, or intrauterine contraceptive devices in combination with preservatives. Or subjects who are using any other method considered sufficiently reliable by the investigator in individual cases.	
Please note that subjects who are surgically sterilized/hysterectomized or post-menopausal for longer than 2 years are not considered as being of child bearing potential.	
· Known or suspected non-compliance, drug or alcohol abuse,	
· Patients with medical history of coronary heart disease (CHD), stroke or peripheral vascular disease (PVD),	
· Patients with medical history of autoimmune disease such as multiple sclerosis, lupus, rheumatoid arthritis, inflammatory bowel disease or small vessel vasculitis,	
· Regular intake of immune-modulating drugs,	
· Inability to follow the procedures of the study, e.g. due to language problems, psychological disorders, dementia or confusional state of the subject,	
· Participation in another study with investigational drug within the 30 days preceding and during the present study,	
· Previous enrolment into the current study,	
· Enrolment of the investigator, his/her family members, employees and other dependent persons.	

Three patients who are at the time point of screening not operable will be treated with re-directed T cells administered into the pleural effusion after completion of 3 cycles of palliative chemotherapy (Figure 3). In the case of one AE grade III/IV or one SAE - both judged to be treatment related by an independent safety monitoring board - the patient number will be expanded to 6 patients. The study will be stopped if one additional DLT occurs also judged to be treatment related.

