Patients will be treated with 1x10^6^ re-directed FAP-specific T cells injected in the pleural effusion. The study ends 35 days after adoptive T cell transfer. Re-directed FAP-specific T cells will be administered at day 0 (day 14 of the third cycle of palliative chemotherapy). The study is designed to demonstrate safety of 1x10^6^ re-directed FAP-specific T cells. The next patient will be enrolled earliest, when the previous patient completed day +14 and the safety monitoring board has not declared any DLTs. The palliative chemotherapy is not part of the study protocol. Due to nature of the study only descriptive statistics will be applied. Means, medians, standard deviations and ranges will be provided for continuous outcomes, and frequencies will be reported for categorical data. The study is approved by the local ethical committee (Kantonale Ethikkommission) of Zurich (KEK-ZH-Nr. 2012/0106), listed at ClinicalTrials.gov (NCT01722149) and in accordance with the Declaration of Helsinki.

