### Study objectives

#### Primary objective

The primary objective is to test safety of a fixed single dose of adoptively transferred FAP-specific re-directed T cells in the pleural effusion. Therefore, all grade III/IV AEs and SAEs will be measured. For the safety assessment, grade III/IV AEs and SAEs will be collected until day +35. The primary safety variables are abnormalities that are judged to be treatment-related and dose limiting toxicity (DLT) by an independent safety monitoring board after the patient passed day +35. Incidence and severity of treatment-related laboratory abnormalities, graded according to National Cancer Institute Common Terminology Criteria for Adverse Events (NCI-CTCAE) version v4.03 criteria as grade III-IV. The protocol will be judged as save when no DLT occurred in the first 3 patients, or not more than 1 DLT in 6 patients.

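### The enrolment gate makes no exception for expansion, so a declared DLT blocks the expansion to 6 and the 1-DLT-in-6 route to a safe verdict

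*Protocol article*

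**What the plan says.** The rules that decide the primary objective appear in three places in the protocol article.

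- **Cohort, expansion and stopping** (Methods/design, General study design, after Table 2). The starting cohort is three: "Three patients who are at the time point of screening not operable will be treated with re-directed T cells". Expansion is triggered as follows: "In the case of one AE grade III/IV or one SAE - both judged to be treatment related" by the independent board, "the patient number will be expanded to 6 patients". Then: "The study will be stopped if one additional DLT occurs also judged to be treatment related".
- **Enrolment gate** (same section, next paragraph): "The next patient will be enrolled earliest, when the previous patient completed day +14 and the safety monitoring board has not declared any DLTs".
- **Verdict** (Primary objective). The protocol is to be "judged as save when no DLT occurred in the first 3 patients, or not more than 1 DLT in 6 patients". DLT status is decided "by an independent safety monitoring board after the patient passed day +35". The Abstract (Methods/design) gives the verdict in nearly the same terms: "The protocol will be judged as save when no DLT occurred in the first 3 patients, or 1 DLT in 6 patients".

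The Abstract also states a staggering rule, but with the day 14 condition only and no mention of DLTs. Nowhere does the article say which rule prevails if the gate and the expansion rule disagree.

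**The concern.** The expansion rule exists for the case of a first treatment-related toxicity. The gate, as worded, closes enrolment in that case. The stopping rule refers to an additional DLT, so the first event is itself regarded as a DLT and patients are expected to be enrolled after it. The gate allows the next enrolment only while the board has declared none.

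At stake is the primary objective of a trial of at most six patients. A board and site facing a first DLT would hold two opposite instructions. If they follow the gate, the trial can end after one or two patients, or after three with one DLT. The zero-in-three limb has then failed and the one-in-six limb cannot be reached, so the trial ends without the answer it was set up to give.

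A smaller point adds to the ambiguity. The expansion trigger is worded as a related grade III/IV AE or SAE, while the gate, the stopping rule and the verdict are worded as DLTs. The word for a further DLT suggests that one event is meant throughout, but the text does not say so.

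**Working it through.** **Logic first.** Suppose a DLT in one of the first three patients is declared before the next enrolment.

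| Rule | Instruction after that DLT |
|---|---|
| Expansion (General study design) | continue to 6 patients |
| Stopping (General study design) | stop only at a further DLT |
| Verdict (Primary objective; Abstract) | 1 DLT in 6 is acceptable |
| Gate (General study design) | do not enrol the next patient |

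The conflict does not depend on whether the gate covers DLTs in any patient or only in the previous one. On the narrower reading, a DLT declared in patient 3 before the next enrolment still bars patient 4, so expansion cannot start. A DLT declared in time in patient 1 or 2 still stops the study there.

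**Size.** The article states no target DLT rate, error rate or operating characteristic, so there is no figure to reproduce. Let p be the per-patient DLT rate (assumed), with patients independent and the expansion event taken to be a DLT.

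- Intended rule: P(safe) = (1−p)³ + 3p(1−p)²·(1−p)³ = (1−p)³ + 3p(1−p)⁵.
- Worst-case gate, where every DLT in the first three blocks the next enrolment: P(safe) = (1−p)³.
- Loss: 3p(1−p)⁵.
- Exactly one DLT in the first three, the situation expansion is meant for: 3p(1−p)².

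At p = 0.2: 0.8³ = 0.512 and 3 × 0.2 × 0.8⁵ = 0.197, which sum to 0.709.

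| Assumed p | Intended P(safe) | Worst-case gate | Loss | Exactly 1 DLT in first 3 |
|---|---|---|---|---|
| 0.05 | 0.973 | 0.857 | 0.116 | 0.135 |
| 0.10 | 0.906 | 0.729 | 0.177 | 0.243 |
| 0.20 | 0.709 | 0.512 | 0.197 | 0.384 |
| 0.30 | 0.494 | 0.343 | 0.151 | 0.441 |

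Enumerating all 2⁶ outcome sequences gives the same P(safe) values.

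**Halt before three patients are treated (worst case).** 1 − (1−p)² = 1 − 0.8² = 0.36 at p = 0.2, and 1 − 0.9² = 0.19 at p = 0.1.

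**Effect of late declaration.** DLTs are formally judged after day +35, while the gate can open at day +14. Let the gate concern only the previous patient, and let f be the share of DLTs declared before the next enrolment (assumed). Then P(safe) = (1−p)³ + (1−f)·3p(1−p)⁵.

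- f = 1: worst case, 0.512 (p = 0.2) and 0.729 (p = 0.1).
- f = 0.5: 0.512 + 0.5 × 0.197 = 0.610 (p = 0.2), and 0.729 + 0.5 × 0.177 = 0.818 (p = 0.1).
- f = 0: the intended rule, no loss.

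If the gate covers DLTs in any patient, late declaration helps less. Patient 6 can follow patient 3 by no less than 3 × 14 = 42 days. A DLT in one of the first three that is ruled on soon after day +35 could therefore still block patient 6.

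**The case against.** The strongest reply is that the intended rule can be read off the page. The expansion rule deals specifically with a first event, and the Primary objective and the Abstract both accept one DLT in six. The gate sentence is a general staggering rule for the ordinary sequence, and the Abstract's version carries only the day 14 condition. A sensible reader would let the specific rule govern and would not end the trial at a first DLT. This stands as evidence of intent, and it is why the defect lies in the wording and not in the design. It does not remove the conflict, because the gate sentence is unqualified and nothing ranks the expansion rule above it.

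Second, a journal article condenses the full protocol, which may say how the board clears resumption. That is fair for missing detail. Here, though, both rules are printed and they disagree.

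Third, the largest losses need every early DLT to be declared before the next enrolment, and neither that share nor the DLT rate comes from the document. This stands: the loss runs from zero to the worst-case column. In addition, a related AE or SAE that triggers expansion without being called a DLT would not close the gate.

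Fourth, the literal gate errs on the cautious side. It exposes no extra patient and cannot create a false safe verdict. That also stands. The harm is an avoidable, inconclusive stop and contradictory instructions at the moment when the board most needs a clear one.

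**Conclusion.** The concern holds. As written, the gate contradicts the expansion rule and closes the one-in-six route to a safe verdict for any DLT in the first three patients that is declared before the next enrolment. In the worst case this costs 0.197 in the probability of a safe verdict at a 20% DLT rate and 0.177 at 10%. On the previous-patient reading with late declaration, the cost shrinks and can reach zero. All of these sizes rest on assumed DLT rates and an assumed timing of declaration. The contradiction itself rests on neither. It should be fixed, as a correction of wording to match the rule the article evidently intends: three patients, expansion to six after one DLT, stop at a second.

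**What to change.** Replace the gate sentence with one that covers the first DLT. For example: the next patient may be enrolled once the previous patient has completed day +14 and the board has reviewed the safety data; after a first DLT, enrolment pauses for board review and may then resume up to a total of six patients; after a second DLT, enrolment stops. Bring the staggering sentence in the Abstract into line.

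Use one event, the board-adjudicated DLT, for the gate, expansion, stopping and verdict, counted as patients with at least one DLT. State that the related grade III/IV AE or SAE in the expansion trigger is that event.

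The cost is protocol wording only. Sample size, dose and assessments do not change.

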### Study objectives

#### Primary objective

The primary objective is to test safety of a fixed single dose of adoptively transferred FAP-specific re-directed T cells in the pleural effusion. Therefore, all grade III/IV AEs and SAEs will be measured. For the safety assessment, grade III/IV AEs and SAEs will be collected until day +35. The primary safety variables are abnormalities that are judged to be treatment-related and dose limiting toxicity (DLT) by an independent safety monitoring board after the patient passed day +35. Incidence and severity of treatment-related laboratory abnormalities, graded according to National Cancer Institute Common Terminology Criteria for Adverse Events (NCI-CTCAE) version v4.03 criteria as grade III-IV. The protocol will be judged as save when no DLT occurred in the first 3 patients, or not more than 1 DLT in 6 patients.

### Secondary objectives

#### Feasibility

Number of patients who received re-directed T cells at day 0 of whom 250 ml of blood were taken at day −21. The study protocol will be declared as feasible when all patients from whom blood was taken, have received transduced T cells.

#### Immune monitoring

Quality of generated re-directed T cells will be tested on day 0. Therefore, frequency assessment of subpopulations of re-directed T cells and assessment of transduction efficacy using flow cytometry will be performed using flow cytometry (monoclonal antibodies: human anti-CD3, human anti-CD4, human anti-CD8, human anti-CD56, human anti-CD28, human anti-CD27, human anti-CD45RA, human anti-CCR7, human anti-IgG). Antigen-specific IFNγ-release after stimulation with FAP expressing cells will be used to test for T cell function. Furthermore, cytotoxicity assays will be performed to determine antigen-specific cell killing after stimulation with FAP expressing cells. The cytokine composition of pleural effusion will be measured at days 0 and +2 by ELISA for IL-2, IL-4, IL-10, TGF-β, TNF-α and IFNγ to assess the local microenvironment. In parallel, the cytokine composition of peripheral serum will be analysed on days −21, 0, +1, +2 and +7 by ELISA for IL-2, IL-4, IL-10, TGF-β, TNF-α and IFNγ. The number of re-directed T cells will be measured in the peripheral blood on days −21, 0, +1, +2, +7 by flow cytometry (human anti-IgG mAB and human anti-CD8 mAB) to assess for lymphocyte migration out of the pleural cavity.

### Dose rationale

This study is designed to show safety of a single dose. Therefore, we do not plan for a dose escalation. We decided to take the lowest dose of re-directed T cell recommended for second generation (CD28 signaling domain) CARs targeting a so far not tested tumor related antigen (FAP) [25]. We will administer 1x 10^6^ re-directed T cells into the pleural effusion.

## Discussion

First-line chemotherapy is the standard treatment option for patients not assessable for surgery. Since palliative first-line chemotherapy results in a median overall survival of 12 months, new therapeutic approaches have to be developed. Therefore, we proposed a concept of loco-regional adoptive transfer of re-directed T cells. We demonstrated target expression of FAP in all subtypes of MPM. Thus, FAP-specific re-directed T cells can be employed in the proposed clinical protocol. The clinical data, so far, using F19 (murine anti-FAP mAB) or sibrotuzumab (humanized F19) showed antibody accumulation in the tumor tissue indicating target specificity [22]. However, the clinical response to both antibody forms was marginal [23]. In contrast to antibodies, re-directed FAP-specific T cells will make use of the specificity of a humanised F19 antibody and combine it with the cytotoxic machinery of CD8 positive effector T cells [26]. Therefore, we expect increased clinical responses [27]. However, the here presented protocol is not intended to proof efficacy.

The main advantage of the loco-regional application of re-directed T cells is the avoidance of immediate systemic side-effects, since the re-directed T cells will not be systemically distributed by blood flow as if administered intravenously. Intravenous application can lead to an interaction of FAP re-directed T cells with off-target tissue leading to immunological mediated toxicity [25]. On-target off-tissue toxicity has to be addressed as first goal. Due to the fact that FAP is expressed in chronically inflamed tissue [28,29], off-target toxicity has to be taken into consideration. Furthermore, FAP expression could be found in fibroatheromata [30]. Therefore, patients with a medical history of autoimmune diseases and/or coronary heart disease, stroke and peripheral vascular disease are excluded from the study. More related to the systemic delivery of T cells, massive cytokine release could be caused by adoptively transferred T cells. There is one report describing an adverse event resulting in the death of a patient after the adoptive transfer of ERBB2 specific re-directed T cells [31]. The cause of death could be partially explained by a cytokine storm. The here presented study is differently designed. Re-directed T cells will not be given intravenously; therefore, a rapid and uncontrolled systemic contact to FAP positive tissue is not likely [32]. The patients are not lympho-depleted by palliative chemotherapy; therefore, clonal competition for cytokines can still take place and lowers the activation of transferred re-directed T cells [33]. Nevertheless, re-directed T cells may expand and migrate outside the pleural effusion and cause in the acute phase anaphylaxis and ARDS within the first 48h. Later on, chronic inflammation can be induced at different sites. Since this trial is the first trial evaluating FAP-specific re-directed T cells in the pleural effusion, all enrolled patients will be treated with the lowest suggested number of cells [25] and monitored for the first 48h at an intermediate care unit.

With the herein presented trial we propose a clinical trial design to test the safety of pre-clinically evaluated FAP specific re-directed T cells for loco-regional intrapleural therapy in patients with MPM.

## Abbreviations

AE: Adverse Event; ARDS: Acute Respiratory Distress Syndrome; CAR: Chimeric antigen receptor; CD: Cluster of Differentiation; DLT: Dose limiting toxicity (DLT); ELISA: Enzyme Linked Immunoabsorbent Assay; ECOG: Eastern Cooperative Oncology Group Performance Status; FAP: Fibroblast activation protein; IFN: Interferon; IL: Interleukin; ICU: Intermediate Care Unit; mAB: monoclonal Antibody; MPM: Malignant pleural mesothelioma; SADR: Suspected adverse drug reaction; SAE: Serious Adverse Event; SUSAR: Suspected Unexpected Serious Adverse Reaction; TAA: Tumor associated antigen; TGF: Tumor growth factor; TNF: Tumor necrosis factor; TpP: Transplantation product.
